## Storage of IMP

The trial drugs (rupatadine and the placebo) will be stored in prepacked envelopes in a designated cupboard at the Centre for Dengue Research.

**9.3 Compliance with Trial Treatment**

The nursing officer who offers the drug to the patient will observe the patient taking the first dose of the drug. The patients will be asked to take the subsequent doses at home. At each daily visit, the participants will be asked if they took the drug. If the patient wishes not to take the drug at any time point in the study he/she will be taken out of the study.

## 9.4 Accountability of the Trial Treatment

Each envelope containing either the placebo or the drug will be marked by a specific number (please see above for randomization and masking). Once a particular envelope is dispersed, the date and serial number it was given to will be recorded.

## 9.5 Concomitant Medication

- Any patients on regular treatment for diseases such as hypertension, diabetes, asthma or any other chronic illness will be asked to take the medication as usual
- They will also take any other medicines such as paracetamol prescribed by the treating physicians as per National Guidelines
- Over the counter medications will not be permitted.

## 9.6 Post-trial Treatment

There will not be any provision to continue use of the drug once the trial ends.

# SAFETY REPORTING

## 10.1 Definitions

| Adverse Event (AE) | Any untoward medical occurrence in a participant to whom a medicinal product has been administered, including occurrences which are not necessarily caused by or related to that product. |
| --- | --- |
| Adverse Reaction (AR) | An untoward and unintended response in a participant to an investigational medicinal product which is related to any dose administered to that participant.  The phrase "response to an investigational medicinal product" means that a causal relationship between a trial medication and an AE is at least a reasonable possibility, i.e. the relationship cannot be ruled out.  All cases judged by either the reporting medically qualified professional or the Sponsor as having a reasonable suspected causal relationship to the trial medication qualify as adverse reactions. |
| Serious Adverse Event (SAE) | A serious adverse event is any untoward medical occurrence that:   - results in death - is life-threatening - requires inpatient hospitalisation or prolongation of existing hospitalisation - results in persistent or significant disability/incapacity - consists of a congenital anomaly or birth defect.   Other ‘important medical events’ may also be considered serious if they jeopardise the participant or require an intervention to prevent one of the above consequences.  NOTE: The term "life-threatening" in the definition of "serious" refers to an event in which the participant was at risk of death at the time of the event; it does not refer to an event which hypothetically might have caused death if it were more severe. |
| Serious Adverse Reaction (SAR) | An adverse event that is both serious and, in the opinion of the reporting Investigator, believed with reasonable probability to be due to one of the trial treatments, based on the information provided. |
| Suspected Unexpected Serious Adverse Reaction (SUSAR) | A serious adverse reaction, the nature and severity of which is not consistent with the information about the medicinal product in question set out:   - in the case of a product with a marketing authorisation, in the summary of product characteristics (SmPC) for that product - in the case of any other investigational medicinal product, in the investigator’s brochure (IB) relating to the trial in question. |

## 10.2 Causality

The relationship of each adverse event to the trial medication will be determined by a medically qualified individuals (DMSB) according to the following definitions:

**Related**: The adverse event follows a reasonable temporal sequence from trial medication administration. It cannot reasonably be attributed to any other cause.

**Not Related**: The adverse event is probably produced by the participant’s clinical state or by other modes of therapy administered to the participant.

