The number of adverse events (AE) were similar in those on rupatadine 40mg and on the placebo and all AE completely resolved (Table 1). Two patients (2.98%) in the placebo group developed a SAE, namely acute liver failure. AE such as hepatitis (ALT>250U/L) was more frequent in those on the placebo as 6 (8.9%) patients developed hepatitis when compared to 3 (4.5%) on rupatadine 40mg. Severe thrombocytopenia (<5×10^9^/L) was seen in one patient in the placebo group. However, thromobocyotopenia and hepatitis are known features of dengue and therefore, unlikely to be due to drugs.

|  | Rupatadine 40mg  N=66 | Placebo  N=67 |
| --- | --- | --- |
| Abdominal pain (%) | 17 (25.7) | 21 (31.3) |
| Vomiting (%) | 21 (31.8) | 21 (31.3) |
| Diarrhoea (%) | 27 (40.9) | 24 (35.8) |
| Hepatitis (%) (ALT>250/L) | 3 (4.5) | 6 (8.9) |
| Low platelet counts  <20 ×10^9^/L (%)  20 to 50×10^9^/L (%) | 12 (18.2)  17 (25.7) | 14 (20.9)  21 (31.3) |
| High ALT (>200 U/L) (%) | 9 (13.6) | 12 (17.9) |
| High AST (>200 U/L) (%) | 14 (21.2) | 18 (26.9) |
| Low white cell count  (<1×10^9^/L) (%) | 0 (0) | 0 (0) |

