**Safety of rupatadine**

In the phase 2 randomized, placebo controlled trial, 40mg of rupatadine was found to be safe and the number of adverse events (AE) were similar in those on rupatadine 40mg and on the placebo and all AE completely resolved. However, the adverse effects on the liver such as development of hepatitis was less in those who were on rupatadine 40mg, when compared to the placebo. In addition, bleeding tendencies were also less. Since both hepatitis and bleeding manifestations are known features of dengue, these clinical features are unlikely to be due to the drugs.

Rupatadine is an orally available second generation antihistamine known to have long acting dual histamine 1 receptor blocking activities and PAF receptor blocking activities for treatment of allergic disease and chronic urticaria (6, 7). Rupatadine has been shown to be well tolerated in many clinical trials in patients who were treated for allergic rhinitis (8, 9), and off-label doses of up to 40mg/day have shown to be well tolerated in chronic urticaria (10). Rupatadine has not shown cardiac adverse effects even at administration of 100mg in healthy individuals (11) (12). It was shown to have less typical side effects of earlier antihistamines such as somnolence, fatigue, headache, impaired memory and learning and sedation (6). A study which determined the effect of rupatadine on those on lorazepam showed that repeated doses of rupatadine had no effect on psychomotor impairment or subjective performance when compared to a placebo (13).

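### Sections 10.1 and 10.2 apply incompatible causality standards, so an event that both rupatadine and dengue could explain is an adverse reaction under one and not *Related* under the other

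*Protocol*

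**What the plan says.** Section 10.1 (Definitions) calls an event an adverse reaction when "a causal relationship between a trial medication and an AE is at least a reasonable possibility, i.e. the relationship cannot be ruled out". It adds that "All cases judged by either the reporting medically qualified professional or the Sponsor as having a reasonable suspected causal relationship" count as adverse reactions. For a serious adverse reaction the same table uses another test: the reporting investigator's belief that the event is due to treatment with reasonable probability.

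Section 10.2 (Causality) gives two categories only. *Related* needs a reasonable time sequence and the condition "It cannot reasonably be attributed to any other cause". *Not Related* reads: "The adverse event is probably produced by the participant’s clinical state or by other modes of therapy administered to the participant". The relationship "will be determined by a medically qualified individuals (DMSB)", which appears to mean the DSMB.

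Section 10.3 follows to resolution or stability those events considered related, as judged by investigators or the sponsor.

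The background shows how attribution was handled in the phase 2 trial. Of laboratory events it says "thromobocyotopenia and hepatitis are known features of dengue and therefore, unlikely to be due to drugs". Under Safety of rupatadine it says: "Since both hepatitis and bleeding manifestations are known features of dengue, these clinical features are unlikely to be due to the drugs".

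**The concern.** The two sections put the burden of proof in opposite places. Section 10.1 asks whether the drug can be excluded as a cause. Section 10.2 asks whether everything except the drug can be excluded. In a population selected for a positive NS1 test, the underlying illness is a competing explanation for many of the events that matter for safety, so the difference is not academic. The background already sets aside hepatitis, thrombocytopenia and bleeding because dengue causes them.

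What is at stake is whether staff can apply the safety section consistently. The adverse-reaction label, the route from SAR to SUSAR, and the duty to follow an event to its end all rest on a causality judgement, and the protocol gives more than one rule for making it.

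**Working it through.** No arithmetic applies: the protocol gives no figure that depends on these definitions. The check is to run the same event through each rule, and then to trace what depends on the result.

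**Step 1. The rules on the same event.**

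| Event | Adverse reaction (10.1) | Category (10.2) |
|---|---|---|
| Drug plausible, dengue and other causes not | Yes | *Related* |
| Both plausible, dengue more probable | Yes, the drug is not ruled out | *Not Related* |
| Both plausible, evenly balanced | Yes | None: dengue is a reasonable alternative, so *Related* fails; dengue is not the probable cause, so *Not Related* fails |
| Drug not a reasonable possibility, dengue probable | No | *Not Related* |

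The rules agree in the first and last rows. They conflict in the second, and section 10.2 gives no answer in the third.

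**Step 2. Whether the middle rows occur in this trial.** The inclusion criteria require a positive NS1 test, so dengue is present in every participant. The protocol itself names overlapping symptoms. Safety of rupatadine lists fatigue and headache among the typical effects of earlier antihistamines (while saying that rupatadine shows less of these effects). Trial Design lists headache, and fatigue after the illness, among the complaints that matter to dengue patients.

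**Step 3. Thresholds and judges.**

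| Place | Threshold | Judge |
|---|---|---|
| 10.1, adverse reaction | Reasonable possibility | Reporting medically qualified professional or sponsor |
| 10.1, serious adverse reaction | Reasonable probability | Reporting investigator |
| 10.2 | No other reasonable cause | DSMB (printed as DMSB) |
| 10.3, follow-up | Considered related, no threshold given | Medically qualified investigators or sponsor |

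Nothing says which prevails. Quality Assurance Procedures schedules the DSMB at half recruitment and mentions no other meeting. If the DSMB is to judge single events, the protocol does not say how it would do so within the 7 and 15 days of section 10.5.

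**Step 4. What depends on the judgement.** Dependent: the adverse-reaction label and SAR status (10.1), SUSAR reporting (10.5, because a SUSAR must first be a SAR), and follow-up to resolution or stability (10.3). Not dependent: recording of adverse events, which 10.3 requires regardless of attribution; reporting of all SAEs to the ERC and SCOCT within 24 hours (10.4); code-breaking, which section 8.4 already triggers on any SAE; and the comparison of side effects between the groups in Description of Statistical Methods.

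**The case against.** The strongest reply is that little is lost in practice. All adverse events are recorded. Every SAE reaches the ERC and SCOCT within 24 hours, which are the two bodies that would receive a SUSAR, and sooner than the SUSAR deadlines. A true excess on rupatadine would show in the counts by arm, whatever label each event carried. The SAR definition has its own test and does not refer to the 10.2 categories, and the follow-up rule in 10.3 names other judges. So it cannot be said that 10.2 controls those steps.

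This stands as a limit on the consequences. It does not remove the contradiction. That SAR and follow-up have their own judges and thresholds is part of the problem, since the reader cannot tell which rule governs.

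A reader might go further and infer that almost every event would be filed as *Not Related*, leaving about zero related events in both arms. The documents do not support that. An event untypical of dengue, such as somnolence, could still be *Related*, and a balanced event falls in no category. The phase 2 percentages, for example diarrhoea in 27 of 66 (40.9%) against 24 of 67 (35.8%), are raw frequencies and not attributions. The background sets aside hepatitis, thrombocytopenia and bleeding only; it does not attribute diarrhoea, vomiting or abdominal pain to dengue, and it does not cite the rule in 10.2.

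A reader might also infer that the whole safety conclusion is biased towards finding no reactions. That does not follow either, because the comparison by arm does not use attribution.

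**Conclusion.** The inconsistency is real and can be seen by reading 10.1 and 10.2 together. For an event that both drug and disease could explain, the protocol gives opposite answers, or in 10.2 none. The SAR threshold and the differing judges add to it.

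Its reach is limited to adverse-reaction labels, SAR and SUSAR classification, any safety statement based on attribution, and which events are followed to resolution. It does not touch the primary endpoint, adverse-event capture, SAE reporting or the comparison between arms. The number of events affected cannot be derived from the protocol.

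The conclusion assumes only that 10.2 is applied as written and that some events have both dengue and the drug as reasonable causes. It is a defect to correct, at a severity below one that would have to be resolved before the trial could be relied on.

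**What to change.** 1. In section 10.2, replace both definitions with the 10.1 standard: *Related* when a causal relation to trial medication is at least a reasonable possibility, *Not Related* when there is no reasonable possibility. This leaves no event without a category.
2. State that being a known feature of dengue is not by itself grounds for *Not Related*.
3. Use the same threshold in the serious adverse reaction definition in 10.1.
4. Name one causality process across 10.1 to 10.3: who judges, whose view prevails on disagreement, and how the judgement is reached within the deadlines of 10.5.

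The cost is a few sentences, a matching change to the adverse event form (annexure 4), and submission of the amendment where approval is needed. The downside is that more events will be classed as related and need follow-up or expedited review. With a reasonable-possibility test and two categories, that could include many common dengue symptoms; the protocol gives no basis for putting a number on it. Attribution should therefore supplement the comparison of all adverse events by arm, which needs no change on this account.

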## 10.3 Procedures for Recording Adverse Events

All AEs occurring during the trial / or until the last date of follow up of the last participant, that are observed by the Investigator or reported by the participant, will be recorded on the AER (annexure 4), whether or not attributed to trial medication. All adverse effects will be notified to ERC FMS, USJ and SCCOT of the National Medicinal Regulatory Authority of Sri Lanka as per time frames and guidelines specified by these bodies

The following information will be recorded: description, date of onset and end date, severity, assessment of relatedness to trial medication, other suspect drug or device and action taken. Follow-up information should be provided as necessary.

The severity of events will be assessed on the following scale: 1 = mild, 2 = moderate, 3 = severe. AEs considered related to the trial medication as judged by a medically qualified investigators or the Sponsor will be followed either until resolution, or the event is considered stable.

## 10.4 Reporting Procedures for Serious Adverse Events

All SAE will be reported to the ERC and the SCOCT within 24 hours from the time the study team, finds out.

## 10.5 SUSAR Reporting

All SUSARs will be reported by the PI to the ERC and to the SCOCT. For fatal and life-threatening SUSARS, this will be done no later than 7 calendar days after the investigators are first aware of the reaction. Any additional relevant information will be reported within 8 calendar days of the initial report. All other SUSARs will be reported within 15 calendar days.

# STATISTICS

## Description of Statistical Methods

The interim analysis will be at half way when half the number of patients are recruited. Statistical significance will be calculated for the interim analysis using the

• χ² test for categorical variables in the two groups

• one-way analysis of variance for continuous variables in the two groups

• Kruskal–Wallis for non-parametric continuous variables in the two groups

• Fisher exact test for categorical variables with small sample size in the two groups ( example when the side effects are small in numbers)

• Intention to Treat (ITT) - ITT analysis will be included as this ignores noncompliance, protocol deviations, withdrawal, and anything that happens after randomization

At the end of the trial, the primary endpoint will be the reduction in the number of individuals who develop DHF. And the secondary efficacy endpoints included duration of reduction in stay at hospitals and side effects. Analysis of covariance (ANCOVA) for the primary endpoint and for secondary endpoints will be used as a statistical method in addition to the above basic statistical methods if applicable. This will be supplemented by a repeated measures analysis.

The effect size will also be computed. Standardized mean difference (SMD), which is used for continuous measures such as leakage, and the number needed to treat, which is used for binary outcomes such as side effects in both groups. The SMD will be computed as the difference between drug and placebo divided by their standard deviation:

SMD = (Drug Improvement - Placebo Improvement) / Standard Deviation

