**Secondary end point**

a. Reduction in complications such as liver failure with use of rupatadine. Liver failure will be diagnosed based on the following criteria. All of the 3 following criteria should be present (16).

- Absence of any previously known liver disease
- A prolonged prothrombin time of 4-6 seconds or more
- A INR of >1.5

b. Reduction in development of shock: Shock will be defined as a pulse pressure of ≤20 mmHg or a drop in the systolic blood pressure of 30mmHg or more

c. Reduction in need of colloids: use of dextran will be considered as the patient having significant fluid leakage as per National Guidelines

d. Reduction in need of blood transfusion/s: as per National Guidelines. Use of even 1 blood transfusion will be considered as the patient having significant fluid leakage

e. Reduction in duration of the illness. The first day of the illness will be defined as the day in which the patient developed fever. The day of recovery will be defined when **all** of the following 3 criteria are fulfilled:

- Patient afebrile for 24 hours
- Platelet counts of >50,000 cells/mm^3^ or a rise of 20% from the lowest value
- Return of the haematocrit to the patients baseline

f. Reduction in sleep disturbances: a reduction in sleep disturbances will be assessed by an eight point scoring system, known as the sleep condition indicator (17). This score assessed, difficulty in falling asleep, waking up in the night, quality of sleep, any effect of poor sleep in concentration, relationships, productivity and general wellbeing. The maximum score attainable is 32 and higher scores indicate better sleep quality.

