# INVESTIGATIONAL MEDICINAL PRODUCT (IMP)

## IMP Description

- The drug will appear as a 10mg tablet
- Patients in the test groups will be given a daily dose of a four 10mg tablets (40mg) orally starting on the day of recruitment for 5 days in addition to the standard treatment as per national guidelines. The control group will receive 4 tablets of the placebo similar to rupatadine for 5 days. Rupatadine will be imported for the study purpose from [name] after approval from SCOCT and NMRA. The placebo will be manufactured by SPMC. The drug and the placebo will be repacked in ensure 5 days of treatment to the study participants.
- As the drug can only be administered orally it will only be given to patients who are able to take drugs orally. At any time point during the study the patient becomes ill and cannot take the drug orally the patient will be taken out of the study. All data collected until the point of withdrawal or until the point of inability to take oral medication will be used in the analysis.
- The placebo will be provided by the State Pharmaceutical Manufacturing Company. The placebo will be identical size and shape to the rupatadine tablet and will not contain ant active ingredients.

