## The Number of Participants

This is planned to evaluate rupatidine drug compared to a placebo in reducing the proportion of patients who develop vascular leak (DHF). The response rate of the active control drug, rupatidine in reduction of fluid leakage by Ultra sound scan was found to be 42.8% (p1) and in the standard treatment was 23.5% (p2). The number of participants per group required to detect a difference in the two groups with a significance level of 5% and a power of 1 - β is 280.

[figure not shown]

Given an anticipated dropout rate of 10% , the sample size needed per group is 280.

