## Inclusion in Analysis

All randomised participants, all dosed participants, all eligible participants will be included. If and when a patient is unblinded that patient will not be included in the analysis. Any data from a patient who is lost to follow up will be included until that point.

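### Duration of illness is a time to recovery, but the tests named for continuous outcomes need a completed duration for every patient, so incomplete follow-up can bias the comparison in either direction

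*Protocol*

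**What the plan says.** **Endpoint.** Under Secondary end point, item e: "The first day of the illness will be defined as the day in which the patient developed fever". The end is set by a sentence that opens "The day of recovery will be defined when" and requires three criteria together: no fever for 24 hours, a platelet criterion, and haematocrit back to baseline. Patient follow up repeats this. Two of the three criteria need a blood count.

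**Methods.** Description of Statistical Methods lists, for the interim analysis, "one-way analysis of variance for continuous variables in the two groups" and "Kruskal–Wallis for non-parametric continuous variables in the two groups". For the end of the trial it adds ANCOVA for the primary and secondary endpoints, on top of those basic tests where applicable, and a supplementary repeated measures analysis. No time-to-event method is named.

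**Patients whose data stop.** Section 8.7 takes patients with prolonged or repeated shock out of the trial. IMP Description takes out those who cannot swallow the tablets, and says: "All data collected until the point of withdrawal or until the point of inability to take oral medication will be used in the analysis". Section 9.3 takes out those who decline the drug. Inclusion in Analysis says: "Any data from a patient who is lost to follow up will be included until that point". The missing-data section only describes missing values. The Number of Participants allows for 10% dropout.

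**The concern.** A patient who leaves before meeting all three recovery criteria has no duration, only a lower bound. ANOVA, Kruskal-Wallis and ANCOVA cannot use a lower bound. The analyst must leave the patient out, which compares only those seen to recover, or enter the days to last contact as if the illness had ended then.

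Loss is unlikely to be unrelated to duration. A longer illness gives more time to be lost, and two of the withdrawal triggers (shock, and inability to take tablets) track severity. If such losses differ between arms, or fall mainly on long illnesses, the estimated effect on duration moves. The two codings also give different answers, and nothing in the protocol fixes the choice before unblinding.

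**Working it through.** The protocol gives no target figure or power for duration of illness, so there is no plan figure to reproduce. What follows illustrates size.

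**Inputs from the protocol.** Background, Table 2 (early recruits): placebo mean 7.1, SD 1.8 days; rupatadine mean 6.3, SD 1.5 days. True difference 7.1 − 6.3 = 0.8 day. 140 per arm (Synopsis). Dropout 10%.

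**Assumptions.** Normal durations; when patients are lost; how loss splits by arm.

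**Notation.** T is the true duration and C the day observation stops. *Dropped* compares the mean of T among patients with T ≤ C. *Counted* compares the mean of min(T, C). *Censored* compares the area under the Kaplan-Meier curve to day 14.

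**Hand check of the counted reading.** If a fraction p of an arm is cut short by d days on average, its mean falls by p × d. So

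counted difference = 0.80 − (p_P × d_P − p_R × d_R).

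Let withdrawal fall evenly between illness day 3 and recovery. Then d_P = (7.1 − 3)/2 = 2.05 and d_R = (6.3 − 3)/2 = 1.65.

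- 10% in both arms: 0.80 − (0.205 − 0.165) = 0.76.
- 15% placebo, 5% rupatadine: 0.80 − (0.3075 − 0.0825) = 0.575.
- 5% placebo, 15% rupatadine: 0.80 − (0.1025 − 0.2475) = 0.945.
- No true effect, 5% against 15%: 0.10 × 2.05 = 0.205 day, in either direction.

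A simulation of 400,000 per arm under the same model gave 0.76, 0.56, 0.94 and 0.20. Loss here does not depend on how long the illness is, and dropping these patients gave 0.79, essentially no bias.

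**Loss concentrated in long illnesses.** Trials of 140 per arm were simulated, with whole-day durations held to days 3–14 and loss on illness days 4–7, either at random or from each arm's longest third. Repeat runs agree to within about 0.02 day.

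| Loss placebo / rupatadine | Dropped | Counted | Censored, restricted mean to day 14 |
|---|---|---|---|
| 10% / 10%, random | 0.80 | 0.74 | – |
| 10% / 10%, longest third | 0.75 | 0.69 | 0.75 |
| 10% / 5%, longest third | 0.67 | 0.57 | 0.72 |
| 5% / 10%, longest third | 0.87 | 0.87 | – |
| 15% / 5%, longest third | 0.54 | 0.39 | 0.65 |

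- Against 0.80, the counted value 0.74 is (0.74 − 0.80)/0.80 = −8%.
- At 10%/5% the errors are −16% (dropped) and −29% (counted); with censoring, −10%.
- At 5%/10% the error is about +9% on both readings.
- Kruskal-Wallis power at 10%/5% is 87–89% (dropped) or 75–80% (counted), against 98% for a log-rank test with censoring. At 5%/10% power does not fall.
- With no true effect and 15%/5% loss from the longest third, a nominal 5% test rejects in 19–22% of trials (dropped) or 41% (counted), against 9% with censoring.

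**The case against.** A reader might infer that the plan prescribes ANOVA for duration of illness. It does not. The line sits in a generic list introduced for the interim analysis and carried forward only where applicable, and the secondary endpoints named in that section are hospital stay and side effects. Duration is reached because it is listed as a secondary endpoint and no other kind of method is offered.

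A reader might also infer that unrecovered patients are dropped or scored as quick recoveries, and that the treatment effect therefore is biased. No section says either. Using data up to the point of loss is also what a censored analysis does, and a statistical analysis plan could settle the coding.

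The amount of incomplete follow-up is unknown too. The 10% was set for the DHF sample size and has no timing, so some of it may come after recovery. Daily visits are meant to catch the day of recovery, and the protocol regards patients discharged from hospital as recovered. The 0.8-day effect comes from 21 + 17 = 38 patients, with p = 0.2. Loss heavier on placebo is one choice; the reverse inflates the effect.

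Finally, censoring does not cure loss related to severity, as the 0.72 and 0.65 in the table show.

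All of this stands and limits the claim to a risk of unknown sign and size. It does not remove the mismatch: the methods the protocol names cannot use an incomplete time, and its own withdrawal rules create such times. The promised intention-to-treat analysis, which sets withdrawal aside, supplies no duration for these patients.

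**Conclusion.** The point holds as a mismatch of method and endpoint, with bias as a risk and not a demonstrated result. Under equal, random loss of 10% the bias is nil if patients are dropped and about 8% of the effect if they are counted as short. Where loss is unequal and falls on long illnesses, a true 0.8 day becomes about 0.57–0.67 (10% placebo, 5% rupatadine) or about 0.87 (the reverse). These figures rest on the earlier trial's means and SDs and on assumed timing and split of loss; the protocol gives neither. Censoring does better than either coding when the heavier loss is on placebo, but does not remove the bias from informative withdrawal. One of six listed secondary endpoints is affected; the primary comparison of DHF is not. The change is worth making because it is cheap and closes a choice between codings that could otherwise be made after the data are seen.

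**What to change.** In Description of Statistical Methods, state that duration of illness is analysed in all randomised patients as time to recovery:

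- Kaplan-Meier curves, a log-rank test, and the difference in restricted mean illness days to day 14 (a recovery hazard ratio may be added).
- Censoring at the last assessment at which the patient had not recovered.
- Death counted as not recovered by day 14.
- A partial duration never entered as a completed one.
- Because withdrawal may be informative, a sensitivity analysis that counts every patient without an observed recovery as unrecovered at day 14.

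Cost: wording and routine analysis, with no new patients or visits. The small downside is that the effect is reported as a restricted mean difference or hazard ratio instead of a simple difference in means.
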